## Abstract

**Introduction:**

Reversing malnutrition-induced impairment of cognition and emotional regulation is a critical global gap. We hypothesize that brain-targeted micronutrient supplemented nutritional rehabilitation in children with moderate acute malnutrition, followed by 2 years micronutrient supplementation will impact on the cognition and emotion regulation of these children.

**Methods:**

The primary outcome of this prospective, randomized controlled trial is to study the development of executive functions (EFs) and emotion regulation (ER) in this cohort. Moderate acute malnourished (MAM; WLZ/WHZ <-2 and ≥-3 z-score, and/or 11.5 cm ≤ MUAC < 12.5cm; n = 140)children aged around one year (11m-13m) in Mirpur, Dhaka, Bangladesh will be randomized (1:1) to receive either locally produced Ready to Use Supplementary Food (RUSF) or Enhanced Ready to Use Supplementary Food (E-RUSF) until anthropometric recovery (WLZ/WHZ > -1SD), or for 3 months after enrollment (whichever is earlier). The randomized MAMs groups will be given either Small Quantity Lipid Based Nutrient Supplement (SQLNS) or Enhanced Small Quantity Lipid Based Nutrient Supplement (E-SQLNS), respectively until the end of the 2-year follow up period. Standard psychosocial stimulation will be provided to the MAMs intervention groups. Biological samples will be collected, anthropometric and neurocognitive assessments will be performed at 2 (22m-26m) and 3 (34m-38m) years of age. Two control groups will be recruited: 1), non-malnourished one-year (11m-13m) old children (WLZ/WHZ score>-1SD; n = 70); and 2) three—year (34m-38m) old children (n = 70) with untreated MAM (WHZ <-2 and ≥-3 z-score, and/or 11.5≤MUAC<12.5 cm). The 3-year-old MAM reference group will be assessed once and provided with 2 months of nutritional rehabilitation support (RUSF Nutriset’s Plumpy’Sup^™^).

## Introduction

### Background and rationale

Nutrition is essential at all stages of life, beginning before birth and continuing throughout childhood. During these periods, critical developmental windows facilitate healthy brain development, including their behavioral correlates (particularly cognitive, motor, and socio-emotional skills [1]. In low- and middle-income countries (LMICs), 45% deaths are due to undernutrition, where around 2 billion survivors suffer long-term cognitive and behavioral consequences [2]. While less than half of all children under-five live in LMICs, nearly 66% of all stunted and 75% of all wasted children live in this region. The highest global prevalence of stunting is found in Asia, with 53% of all stunted children, and 70% of all wasted children located in Southern Asia [3, 4], making this region a high priority for intervention. Since 2000, stunting has steadily declined but a high prevalence of wasting persists hindering the achievement of Sustainable Development Goal 2: zero hunger targets by 2030 [5, 6], an important marker for development in this region.

Bangladesh, situated in the Indian subcontinent bordering the Bay of Bengal, is amongst the most densely populated countries globally [7]. Malnutrition is a significant health issue, with approximately one-third of preschool-age Bangladeshi children being stunted (low height-for-age), ≥ one-fifth are underweight (low weight-for-age) and approximately one-tenth are wasted (low weight-for-height) [8–10]. In Bangladesh, approximately 1.8 million children under 5 years of age suffer from Moderate acute malnutrition (MAM) [11–13], diagnosed as weight-for-height (WHZ) or weight for length (WLZ) z-scores between <-2 and ≥-3 of WHO child growth standards and/or mid upper arm circumference (MUAC) <12.5 and ≥11.5 cm [14, 15].

Malnourished children have multiple micronutrient and macronutrient deficiencies and exhibit an abnormal gut microbiota [16], which can disrupt the bidirectional neural and immune interactions between the gut and brain by affecting signal molecules produced by the microbiota (e.g. short-chain fatty acids, and neurotransmitters) [17]. Nutritionally wasted children exhibit brain atrophy on MRI, and while re-feeding reverses the shrinkage of the brain, significant brain microstructural and functional deficits persist [18]. The anatomic reconstitution of the brain with feeds designed principally for rapid physical catch-up growth might result in atypical cognitive and emotional performance. Correcting cognitive and emotion regulation outcomes after malnutrition requires providing the appropriate nutrients in amounts to support rapid catch-up growth of both the body and brain.

The human brain develops from prenatal life through early childhood, with a crucial developmental window between birth and age 3 years [19]. Malnutrition, which includes nutrient deficiencies, and gut microbiome dysbiosis can induce structural and functional abnormalities of the brain that lead to lifelong neuropsychological sequelae [20, 21]. Improving brain recovery in malnourished children might require augmented feeds with key nutrients that have targeted functionality in the brain, particularly during periods of rapid development.

## Methods

### Study setting

This study is a community based randomized controlled clinical trial, conducted in the Mirpur area of Dhaka, Bangladesh. Mirpur is divided into five zones, with a population of approximately half a million people. The area is densely populated, with > 38,000 people living in each square kilometer [22], in contrast to Tokyo which has 7,330.6 persons per square kilometer. The Dhaka cohort represents a typical urban-poor population exposed to poor living and sanitary conditions, environmental hazards, toxins, and poor access to nutrition.

All clinical activities will be conducted at the Mirpur field clinic, which is located in ward 5, in close proximity to the participants. This clinic has been a research site for nearly 30 years.

This study protocol was registered on clinicaltrials.gov on November 29, 2022 (study ID number: NCT05629624) and was produced in compliance with the Standard Protocol Items: Recommendations for Interventional Trials (SPIRIT). See Fig 1 summarizing the schedules of enrollment, interventions and assessments of the study (S1 Checklist).

**Fig 1 pone.0296529.g001:**
[figure not shown]
SPIRIT schedule. Schedules of enrollment, interventions and assessments.

### Objectives and trial design

We propose an enhanced nutritional intervention to investigate the impact of enriching the diet with micronutrients and prebiotics during recovery from MAMs on executive functions (EFs) and emotion regulation (ER). This intervention will be combined with psycosocial stimulation. The study cohort will be recruited within the Mirpur locality in Dhaka city, Dhaka North City Corporation (DNCC) wards 2, 3 and 5.

Our primary outcome is to study the development of EFs and ER in this cohort. The secondary outcomes are to assess whether nutritional interventions and psychosocial stimulation improve executive dysfunction (EDF) and emotion dysregulation (EDR) upon recovery from childhood moderate acute malnutrition. We will identify features of microbiome assembly, metabolomics, and child genetics that respond to nutritional intervention and contribute to executive and emotion regulation/dysregulation in healthy Bangladeshi children. The findings from this study will identify the effects of nutritional intervention and psychosocial stimulation on EF and ER in malnourished children, thereby offering valuable insights for scalable approaches to improve these aspects of child development.

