### Control groups

Two control groups will be recruited. The first control group will consist of non-malnourished children who are recruited at the same age (11 months to 13 months old) as the MAM intervention group children.

The second control group (i.e. outcome reference group) will be a MAM reference group consisting of children who are 3 years (34 months to 38 months old) who present with previously untreated MAM. See Fig 2 demonstrating the flow of recruitment process of the study participants.

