### Allocation

After recruiting MAM children they will be randomized 1:1 into two groups: Group A and Group B (Table 2). Computer generated randomized sequences will be used to allocate these children into different groups. The randomized sequences will be generated by a study investigator who will not be directly involved in assigning intervention during enrolling the participants to avoid bias. These sequences will be sealed in white opaque sealed envelopes and will be opened in front of the mother or legal guardian once they consent for the child by the study physician.

**Table 2 pone.0296529.t002:** Intervention scheme.

Group			Number	Intervention
Control group Non malnourished children at 1 year ± 1m (WLZ >-1 SD)			70	No nutritional and psychosocial intervention. Only follow-up
Intervention group (n = 140) With WLZ <-2 and ≥-3, and/or MUAC <12.5 and ≥11.5 cm having MAM at 1year ± 1m	Randomization Into two groups	Group A	70	500 kcal/day RUSF daily till WLZ >-1 achieved or for a maximum of 3 months and then SQ-LNS will be provided for up to the end of the study period. Psychosocial stimulation
		Group B	70	500 kcal/d Enhanced WLZ >-1 achieved or for a maximum of 3 months and then E-SQLNS will be provided for up to the end of the study period. Psychosocial stimulation
Outcome Reference group With WHZ <-2 and ≥-3 z-score, and/or MUAC <12.5 and ≥11.5 cm having stable MAM at 3 years ± 2m			70	After completing the baseline assessment, participants will be provided with daily RUSF (Nutriset’s Plumpy’Sup^™^, RUSF) for 2 months and referred to NRU at icddr,b or local facilities if needed.

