### Psychosocial stimulation

Standard psychosocial stimulation will be provided to the MAM intervention groups. Psychosocial stimulation will consist of bi-weekly, set stimulation curriculum “REACH-UP”. The Reach Up curriculum is a semi-structured, culturally relevant child-age appropriate curriculum that addresses key components of the “nurturing care framework” to promote optimum development [33]. The developmental tasks will take place within a playful environment rather than a work-focused one. During home visits, health-workers will demonstrate to mothers how to play with home-made toys and books and interact with their children aimed at fostering their growth and development.

Toys will be given to the child to play with and learn from, until the next visit, when a new set of developmentally appropriate toys will be provided. The activities in the curriculum are ordered by difficulty level and the health workers will be trained to choose the level for each child according to their ability to do the activities.

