### Neuropsychological assessment

Neurodevelopmental assessment data for the control and intervention groups will be collected at enrollment (1year ± 1m), 2years ± 2m, and at 3 years ± 2m. Neurodevelopmental assessment data for the outcome reference group will be collected only at enrollment.

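### Both randomised arms receive a supplement and the same psychosocial stimulation, so the trial can identify only enhanced versus standard feeds, not the effects of stimulation or of feeding

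*Protocol article*

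**What the plan says.** Objectives and trial design contains two aims of different breadth. The narrower is to "investigate the impact of enriching the diet with micronutrients and prebiotics during recovery from MAMs". The broader appears as a secondary outcome, to "assess whether nutritional interventions and psychosocial stimulation improve executive dysfunction (EDF") and emotion dysregulation, and again in the closing sentence: "The findings from this study will identify the effects of nutritional intervention and psychosocial stimulation on EF and ER in malnourished children". The Discussion repeats the broader aim.

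On allocation, the protocol says of the MAM children that "they will be randomized 1:1 into two groups: Group A and Group B". Table 2 gives Group A "500 kcal/day RUSF daily till WLZ >-1 achieved or for a maximum of 3 months", then SQ-LNS. Group B receives the enhanced feed at the same daily energy, then E-SQLNS. Table 2 lists stimulation in both rows, and the section on it agrees: "Standard psychosocial stimulation will be provided to the MAM intervention groups".

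Two further groups are not randomised. The well-nourished controls enter at 11-13 months and receive no intervention. The other is a "MAM reference group consisting of children who are 3 years (34 months to 38 months old) who present with previously untreated MAM". For that group, "Neurodevelopmental assessment data for the outcome reference group will be collected only at enrollment", and its feeding starts only after that assessment.

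**The concern.** A randomised trial identifies the effect of what differs between its arms. Stimulation does not differ, and neither does the presence of a supplement. The broader aim therefore has no randomised comparison behind it.

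An untreated MAM comparator could be sought only in the 3-year reference group, which differs from the treated cohort in how and when its children were selected and in how often they have been tested. The article presents its findings as a guide to scalable approaches. A statement that stimulation or feeding improved executive function (EF) or emotion regulation (ER) could therefore carry weight that the design does not give it.

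**Working it through.** **1. The plan's own figure.** Sample size gives 51 per group at 80% power, one-tailed 5%. Reading medium as 0.5 SD, n = 2(1.645 + 0.842)²/0.5² = 49.5, so 50 per group. The exact t-test gives 50.15, rounded up to 51, so the figure reproduces. (Sample size also equates medium with 2 SD, which would give 4 per group; that is a separate matter.) The comparison powered is well-nourished versus wasted children. It is neither Group A versus Group B nor a test of stimulation.

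**2. What each group receives** (Table 1, Table 2, Dietary intervention, Psychosocial stimulation, Neuropsychological assessment).

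| Group | Randomised | Selected on | Any feed F | Enhancement E | Stimulation S | Scheduled neurodevelopmental assessment at age 3 |
|---|---|---|---|---|---|---|
| A | yes | MAM at 11-13 months | 1 | 0 | 1 | third |
| B | yes | MAM at 11-13 months | 1 | 1 | 1 | third |
| Well-nourished | no | WLZ/WHZ > -1 at 11-13 months | 0 | 0 | 0 | third |
| 3-year reference | no | MAM at 34-38 months | 0 when tested | 0 | 0 | first and only |

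**3. What can be estimated.** Write the expected outcome in a MAM child as μ + f·F + e·E + s·S. Then B - A = (μ + f + e + s) - (μ + f + s) = e. Both f and s cancel. If the components interact, B - A is still only the effect of enhancement when feed and stimulation are both present. No analysis of the two arms recovers f or s, because neither F nor S varies.

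**4. What the reference group adds.** A - reference = f + s + selection difference + practice difference. Even if the last two terms were zero, this would give the sum f + s and not either part.

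They cannot be assumed zero. Treated children were selected for MAM about two years before the age-3 outcome, and Dietary intervention keeps them in the study whether or not they recover. Reference children must have MAM at the time they are tested, so children who had MAM at 1 year and recovered unaided are absent. Table 1 does not require reference children to have had MAM at 1 year.

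**5. Possible size of the selection term, with no treatment effect.** These inputs are assumptions, not taken from the documents: WLZ normal with mean -0.75 and SD 1 at both ages; correlation r between ages 1 and 3 of 0.3 to 0.7; EF changing by b = 0.1 to 0.3 SD per SD of WLZ; selection on WLZ only, ignoring MUAC and practice effects.

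In standardised units MAM is the interval -2.25 to -1.25. The mean within it is m = -(0.18265 - 0.03174)/(0.10565 - 0.01222) = -1.615. The difference, treated cohort minus reference, is then:

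- EF driven by WLZ at age 3: b(r·m - m) = 1.615·b·(1 - r). The range is 1.615 × 0.1 × 0.3 = +0.05 to 1.615 × 0.3 × 0.7 = +0.34 SD.
- EF driven equally by WLZ at both ages: 0.
- EF driven by WLZ at age 1: b(m - r·m), that is -0.05 to -0.34 SD.

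A simulation with 4 million children gave the same values.

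**The case against.** The strongest defence is that the article already states the narrower aim, which Group A versus Group B answers. A nutritional effect is therefore identified, and the closing sentence can be read as describing a package rather than promising to isolate stimulation. The first part stands, and the fix keeps that comparison. The second does not rescue the sentence: no randomised arm lacks the package, so its effect is not identified either.

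A second defence is that the article specifies no efficacy test of treated against reference children. Data analysis plan speaks of wasted and non-malnourished cohorts. This stands too. That use is inferred from the label outcome reference group and from the absence of any other untreated MAM comparator.

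A reader might infer more: that the reference group biases the comparison toward benefit, so that the secondary objective would be answered favourably with no effect at all. One could attach numbers. If current wasting carries a 0.5 SD gap and a share x = 10% to 50% of untreated children remain wasted at 3, the spurious benefit is (1 - x) × 0.5 = 0.45 to 0.25 SD. The documents do not support this reading:

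- The persistence range appears nowhere in them.
- The 0.5 SD is inferred from n = 51. It refers to children with WLZ/WHZ above -1, so a child who has only risen to between -2 and -1 would not be expected to regain all of it.
- The calculation assigns the whole gap to current wasting. The Background describes a crucial developmental window from birth to age 3 and deficits that persist after re-feeding, which leaves room for lasting effects of early wasting and so for a zero or reversed bias.

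The absence of an untreated criterion from Table 1 is minor, since Control groups states it. Recruitment nevertheless ties final eligibility to Table 1, so the two should agree.

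**Conclusion.** The concern holds as an overclaim about what the design identifies. That neither stimulation nor feeding versus none can be estimated from the randomisation follows from Table 2 alone and needs no outside figure. A later analysis plan could not repair it, because the allocation scheme fixes it. What is identified is the enhanced versus the standard supplement regimen, with Reach Up in both arms.

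Comparisons of treated children with the 3-year reference group are open to selection and practice-effect bias. Toward benefit is plausible, because recovered children remain in the treated cohort and those children have been tested before. The sign and size are not established: the range of -0.34 to +0.34 SD rests wholly on the assumptions in the working and shows only that the bias could be material. The wording should be corrected; the randomised comparison itself is unaffected.

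**What to change.** - Restate the secondary objective and the closing claim of Objectives and trial design as the effect of E-RUSF/E-SQLNS versus RUSF/SQ-LNS, with Reach Up given in both arms. Align the matching sentence in the Discussion.
- Drop any claim to identify the effect of stimulation, or of feeding versus no feeding.
- Label every comparison with the well-nourished controls and the 3-year reference group as descriptive, with no efficacy conclusion. Setting the reference group against the controls at age 3 does not avoid the problem: those controls were selected at 11-13 months and are on their third assessment.
- Reconcile the untreated status given in Control groups with the reference-group column of Table 1.

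Enrolment began in February 2022, so this is a protocol amendment rather than an editorial correction. It changes no participant's care and no data collection. The trial gives up only a claim that its design cannot support.

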### Recruitment

Enrollment was initiated on February 7, 2022 and will continue until February 2024.

Study surveillance workers (SWs) conducted a door-to-door census (~ 100,000 households) in Mirpur DNCC wards ward 2, 3 and 5 between January and December 2022. The primary focus of the census was to compile a list of babies aged 11 to 13 months and 34 to 38 months. Verbal consent was obtained to participate in the census. The census identified 5,736 children aged between 11 to 13 months and 2,314 children aged between 34 to 38 months. During the census, if the guardian verbally consented to the study procedure, and the babies met the inclusion and exclusion criteria of the study (Table 1), the SWs proceeded to measure the mid-upper arm circumference (MUAC) of the child. We are inviting mothers of the babies who are within the expected MUAC range to visit the study clinic for further assessment and enrollment.

**Table 1 pone.0296529.t001:** Eligibility criteria.

Intervention group	Control group	Outcome reference group
1 year MAM (n = 140)	1 year well-nourished (n = 70)	3 years MAM (n = 70)
*Inclusion Criteria*:		
Child aged between 1year ± 1m (11m–13m).	Child’s aged between 1 year ± 1m (11m–13m).	Child aged between 3 year ± 2m (34m–38m).
Child’s WLZ/WHZ score is <-2 and ≥-3, and/or MUAC <12.5 and ≥11.5 cm. Child is free from any acute illness.	Child’s WLZ/WHZ score is > -1 SD, Child is free from any acute illness.	Child’s WLZ/WHZ score is <-2 and ≥-3, and/or MUAC <12.5 and ≥11.5 cm. Child is free from any acute illness.
Mother is willing to sign informed consent form.	Mother is willing to sign informed consent form.	Mother is willing to sign informed consent form.
*Exclusion Criteria*:		
Child aged > 13 months or < 11 months.	Child aged > 13 months or < 11 months.	Child aged > 38 months or < 34 months.
Child has any congenital anomaly.	Child has any congenital anomaly.	Child has any congenital anomaly.
Mother is unwilling to sign informed consent form.	Mother is unwilling to sign informed consent form.	Mother is unwilling to sign informed consent form.
Mother unwilling to bring child to the clinic for assessments or to use intervention feeds on child.	Mother unwilling to bring child to the clinic for assessments	Mother unwilling to use the rehabilitation feed on child or the small quantity supplement.

Final screening for eligibility and study consent will occur at the Mirpur study clinic (S1 File). Because the primary study population is incapable of assenting, due to age 1year ± 1m and 3 years ± 2m, parental permission will be obtained for study participants. The consenting process will be done by a study physician. The consenting process will be tailored to each mother’s literacy level and will involve reviewing the inclusion and exclusion criteria. Comprehension of the study will be assessed using scripted points and open-ended questions. After obtaining consent, the clinical screening team will proceed with anthropometric screening of the child and mother.

Following consent, the clinical screening team will complete a screening form (Supplementary materials 1), capturing the date of visit, sex, date of birth (DOB), weight (in kg), length/ height (in cm), head circumference (in cm), and MUAC (in cm) measurements of the child. The team will calculate the WLZ/WHZ Z-score for the child using the WHO anthropometric calculator. The child’s age will be validated using the EPI vaccination card.

Final enrollment eligibility is based on matching the Z-score and other physical examination findings with the eligibility criteria (Table 1).

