### Sample size

Power for comparisons between well-nourished (WLZ/WHZ > -1 SD) and wasted children (-3≤ WLZ/WHZ <-2 z-score, and/or 11.5≤ MUAC <12.5 cm) at 1 and 3 years was estimated using the Student’s t-test and Structural Equation Modeling (SEM). For the t-test, the proposed medium level difference between the two groups (i.e. 2 standard deviation) requires a minimum of 51 participants per group for power equal to 80% using a level of significance equal to 5% (for a one-tailed test).

Sideridis et al. 2014 [23] used a series of Monte Carlo simulations to estimate that 50–70 participants would suffice to evaluate functional connectivity in the brain using EF, EEG or fMRI. Sideridis et al.’s simulation involved medium sized models (i.e. 7 latent variables), but the model size is inversely related with sample size. Therefore, larger models, like those in the present study, require fewer participants.

To account for participant drop out during the follow-up period, sample sizes were increased to n = 70 children in each group.

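### The control rule in Table 1 has no MUAC condition, so a child who counts as MAM on MUAC alone can also qualify as a well-nourished control

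*Protocol article*

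**What the plan says.** **Control group.** The control column of Table 1 (Recruitment) requires "WLZ/WHZ score is > -1 SD, Child is free from any acute illness" and sets no MUAC limit. The rule recurs in the same form in the Abstract, in Table 2 under Allocation ("Non malnourished children at 1 year ± 1m (WLZ >-1 SD") and under Sample size ("comparisons between well-nourished (WLZ/WHZ > -1 SD) and wasted children"). The section Control groups describes these children so: "The first control group will consist of non-malnourished children who are recruited at the same age (11 months to 13 months old").

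**MAM intervention group.** Table 1 requires "WLZ/WHZ score is <-2 and ≥-3, and/or MUAC <12.5 and ≥11.5 cm", so either index alone is enough. Background and rationale defines MAM with the same alternative: "and/or mid upper arm circumference (MUAC) <12.5 and ≥11.5 cm".

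**Exclusions.** Table 1 lists age, congenital anomaly, consent and willingness to take part. None of them mentions MUAC or WLZ.

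**Final decision.** Recruitment states: "Final enrollment eligibility is based on matching the Z-score and other physical examination findings with the eligibility criteria (Table 1").

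**Recovery.** Table 2 gives Group A "500 kcal/day RUSF daily till WLZ >-1 achieved or for a maximum of 3 months". The Dietary intervention section applies the same WLZ threshold and the same maximum period to Group B.

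**The concern.** Two groups that are to be compared as malnourished and not malnourished should have entry rules that no child can meet together. Here one group is defined on two indices and the other on one of them, and nothing says where a child who meets both rules belongs.

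At stake is the comparison of well-nourished with wasted children, which is the one that Sample size powers. If children with low MUAC enter as controls, the control mean moves towards the MAM mean. If children with WLZ above -1 enter the MAM group through MUAC and perform like controls, the MAM mean moves the other way. Either shift shrinks the observed difference.

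A second matter lies within the MAM rule. The cut-off that defines a control, WLZ above -1, also defines recovery. A MAM child who enters on MUAC with WLZ above -1 has met the recovery criterion before the first feed.

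**Working it through.** **1. Apply the printed rules to example children.** MAM rule: (-3 ≤ WLZ < -2) or (11.5 ≤ MUAC < 12.5). Control rule: WLZ > -1.

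| WLZ | MUAC (cm) | MAM rule | Control rule |
|---|---|---|---|
| -0.5 | 12.0 | met | met |
| -0.5 | 11.0 | not met | met |
| -0.5 | 13.0 | not met | met |
| -1.5 | 12.0 | met | not met |
| -2.5 | 11.0 | met | not met |
| -3.5 | 12.0 | met | not met |

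Row 1 is the overlap. Row 2 is a child below the MUAC band who can enter only as well-nourished. Rows 5 and 6 are moderate on one index and below the stated floor on the other. No printed exclusion covers any of these four rows.

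**2. Reproduce the plan's sample size.** Inputs from Sample size: one-tailed 5%, 80% power, a medium difference, two-sample t-test. With d = 0.5 the normal approximation is n = 2(1.645 + 0.842)²/0.5² = 49.5, so 50 per group. The noncentral t distribution gives 51 per group with power 0.806, which is the stated figure. At 70 per group, power is 0.903. (The text also calls the difference 2 standard deviations. That would need only 4 per group, so 51 fits d = 0.5 only. This mismatch is a separate issue.)

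**3. How many children could be affected.** The article gives no WLZ or MUAC distribution, so every input here is an assumption: bivariate normal, WLZ mean -1.0 to -0.7 and SD 1.1, MUAC mean 13.6 to 13.9 cm and SD 1.0, correlation 0.60 to 0.85. Simulating 2 million children per setting gives:

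- Children with WLZ > -1 whose MUAC lies in the 11.5 to 12.5 cm band: 0.1% to 4.4%. At most 0.044 × 70 = 3.1, or about 3 of 70 controls.
- MAM-eligible children with WLZ > -1: 0.2% to 14.5%, that is 0.002 × 140 = 0.3 to 0.145 × 140 = 20.3, or 0 to 20 of 140.
- MAM-eligible children below the floor on the other index: 7.3% to 12.4%, that is 0.073 × 140 = 10.2 to 0.124 × 140 = 17.4, or 10 to 17 of 140.

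**4. Effect on power.** If a share f of one group scores like the other group, the expected difference is d = 0.5(1 - f). The increase in spread from mixing is ignored.

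| Where the overlap sits | f | d | Power, 51 per group | Power, 70 per group |
|---|---|---|---|---|
| None | 0 | 0.500 | 0.81 | 0.90 |
| Controls, worst case | 0.044 | 0.478 | 0.77 | 0.88 |
| MAM group | 0.10 | 0.450 | 0.73 | 0.84 |
| MAM group, worst case | 0.145 | 0.4275 | 0.69 | 0.81 |

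The MAM rows assume that children who enter on MUAC with WLZ > -1 score exactly like controls. That is the least favourable assumption for those rows. The article neither supports nor excludes it.

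**The case against.** The strongest reply is that the labels close the gap. The article makes MUAC below 12.5 cm diagnostic of MAM and calls the controls non-malnourished, so a careful physician would not enrol such a child as a control. MUAC is taken at the census, invitation depends on it, and it is taken again at the clinic. The flow chart and screening form are not at hand and may carry the missing condition. This is fair evidence of intent, but it does not remove the overlap. The MUAC range that triggers invitation is neither defined nor given by group, and final eligibility refers back to Table 1. The WLZ-only rule also stands in four places. This is a stated rule that is wrong, not a detail left to a fuller document.

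It is also fair that the simulation describes a general population, whereas recruitment here was filtered on MUAC. The true shares could be higher or lower.

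Three stronger readings are tempting, and the documents do not support them:

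- *The entry rule admits children outside the article's own definition of MAM.* It does not. Background and rationale uses the same alternative wording, so a child in the moderate band on one index is MAM as defined. What remains is that the child may be below the floor on the other index with no exclusion printed.
- *The comparison of Group A with Group B is compromised.* Both arms share one entry rule, so its internal validity holds. Dilution is limited too: a child who meets the recovery criterion at entry loses at most the 3-month feeding phase, while SQ-LNS versus E-SQLNS continues to the end of the 2-year follow-up.
- *Malnourished children have been enrolled as controls.* The article shows only that the printed rule permits it.

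**Conclusion.** The point holds as a defect in the control rule. As printed, the control and MAM criteria overlap for WLZ above -1 with MUAC from 11.5 to below 12.5 cm, and a child with MUAC below 11.5 cm can qualify as well-nourished. Both results contradict the group's label and the article's definition of MAM.

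The effect on the controls is probably small: on the assumed distributions at most about 3 of 70, with power at 70 per group falling from 0.90 to about 0.88. The MAM side could matter more, with 0.2% to 14.5% of eligible children having WLZ above -1, but that range is too wide to support a definite claim. All these figures rest on assumed distributions. The logical overlap does not.

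Two inconsistencies in the MAM rule stand beside this: entry on MUAC can coincide with a recovery criterion already met, and a child moderate on one index can be below the floor on the other. The passages concerned must be reconciled. Which clinical rule should apply is not for this review.

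**What to change.** 1. Add a MUAC condition to the control column of Table 1: not below 12.5 cm, which is the article's own upper limit for MAM. Repeat it in the Abstract, Sample size and Table 2.
2. For children already enrolled, count from the screening WLZ and MUAC how many fall in the overlap, and how many controls have MUAC below 11.5 cm. Report both counts by group.
3. Specify a sensitivity analysis of the MAM versus control comparison that excludes or reclassifies these children. Exclusion is cleaner after baseline, because a reclassified control will have had no intervention. Randomized children stay in their allocated arm for the comparison of Group A with Group B.
4. Have the sponsor's clinicians reconcile the MAM entry rule in Table 1 with its lower limits on the other index, and with the WLZ-only recovery criterion in Table 2 and Dietary intervention.

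The cost is low. The wording change is one clause, and both measurements are already on the screening form, so no new data are needed. Enrolment began in February 2022 and was planned to run until February 2024, so the new wording cannot reach children already enrolled. For them, only steps 2 and 3 help. With mutually exclusive groups, the planned 51 per group at d = 0.5 does not change.
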